### Procedure for unblinding if needed

Treatment assignment will be disclosed to trial participants only upon their completion of the study.

### Intervention descriptions

Training sessions will commence within 1-week after baseline #2 assessments. To help reduce impedances, subjects were asked to arrive with non-braided, dry, clean (i.e. no conditioner, gels, pastes, or sprays) hair. Participants will attend three 30-min sessions per week, every other day, over 4 consecutive weeks (12 sessions in total). 19-channel sLORETA ISF-NFB training will be performed using a DC coupled amplifier produced by Brainmaster Inc. and the BrainAvatar software (version 4.7.5.844) in a quiet, cool (~15°C), dimly lit room by an unblinded male researcher with >2 years of experience in the administration of NFB. Participants will be seated in a comfortable chair and an appropriately sized Comby EEG cap will be placed on the participant’s head. Using a blunt need and syringe, the scalp will be mildly abraded prior to the application of an electrolyte gel beneath each electrode. It should be noted that the purpose of the cool room and scalp abrasion is to mitigate contamination of the EEG signal by electrodermal (i.e. sweat gland) potentials which are known to mimic brain-derived eISFs [63, 69]. Nineteen-channel EEGs will be recorded with the silver/silver chloride (Ag/AgCl) electrodes positioned according to the International 10–20 system (i.e. Fp1, Fp2, F3, F4, C3, C4, P3, P4, O1, O2, F7, F8, T3, T4, T5, T6, Fz, Cz, Pz) using a linked mastoids reference and a ground electrode positioned centrally between F3, Fp1, Fz and Fpz. The impedances of the active electrodes will be kept below 10 kΩ and a 50 Hz notch filter will be set.

Immediately prior to each training period, a demonstration of motion artefact alerts will be performed with instructions to avoid eye/head/face movements to minimize this non-rewarding feedback. Participants will then be instructed to close their eyes, relax, stay awake, and listen to the sound being played. They will be informed that the sound they hear reflects that they are doing well. Notably, no explicit strategies or instructions were given as, with few exceptions [204], implicit strategies have been shown to produce better outcomes [205–210].

Continuous, real-time auditory feedback will be used for reinforcement and produced within 30 ms of the subject’s eISFs (0.0–0.1 Hz) within the pre-defined ROIs (i.e. dACC and/or PCC; Fig. 1) surpassing the threshold(s). These ROIs were selected because, as outlined in the introduction, they are considered key cortical nodes within the core RSNs which are consistently found to be disrupted in ID populations. sLORETA permits the selection of any cortical region for feedback of the current density using voxels selected based on Montreal Neurological Institute (MNI) coordinates [211]. For a complete list of targeted voxels for this trial, see Additional files 1 and 2.

**Fig. 1 Fig1:**
[figure not shown]
Targeted regions-of-interest (ROIs). Abbreviations: dACC, dorsal anterior cingulate cortex; PCC, posterior cingulate cortex. Note: red dot indicates salience network (SN), and blue dot indicates the default mode network (DMN) node

The reward threshold(s) will be manually adjusted in real-time to maintain a 60% ± 10% success rate. Manual, rather than automated, thresholding was chosen as it has been reported to lead to better EEG-learning [125, 173, 206, 208]. The yoked-sham sessions will be identical to active sessions, including live EEG recordings and real-time motion/EMG artefact alerts, however, the auditory rewards will derive from playbacks of genuine ISF-NFB sessions from another female ID participant at the same training stage recorded via free, open-source Audacity software [212] which uses the computer’s sound card as an audio to digital converter. Importantly, this type of control allows matching of rewards and performance across sham and genuine conditions, thereby controlling as much as possible the learning context and degree of motivation [213] while theoretically severing the operant conditioning aspect of EEG-NFB. Additionally, it has been reported that training effects are more robust when the clinician is present [214], therefore, irrespective of group assignment, the trainer will be present for the duration of all sessions. Further, the trainer will monitor the participants’ protocol adherence. A detailed description of the trial intervention using the Template for Intervention Description and Replication (TIDieR) [215] has been provided in Table 1.

**Table 1 Tab1:** Template for Intervention Description and Replication (TIDieR)

Item number	Item	Description
1.	**Brief name** Provide the name or a phrase that describes the intervention.	Infraslow closed-loop brain training for Anxiety & Depression (ISAD)
2.	**Why** Describe any rationale, theory, or goal of the elements essential to the intervention.	Electrophysiological infraslow (<0.1 Hz) fluctuations (eISFs) are believed to coordinate and integrate information exchange within and between core-intrinsic connectivity networks (ICNs). Further, communication within and between core-ICNs has been found to be disrupted in internalizing disorder (ID) populations. We hypothesize that eISF neurofeedback (ISF-NFB) targeting key cortical nodes of these core-ICNs, may restore proper intra- and inter-network function and reduce ID-related symptoms.
3.	**What** Materials: Describe any physical or informational materials used in the intervention, including those provided to participants or used in intervention delivery or training of intervention providers. Provide information on where the materials can be accessed (e.g. online appendix, URL).	19-channel sLORETA ISF-NFB training will be performed using a DC coupled amplifier (Brainmaster Technologies Inc.), ASUS laptop computer (ASUSTek Computer Inc.; 64.0 GB RAM; Intel Core i7 processor) running BrainAvatar software (version 4.7.5.844), 24 (Ag/AgCl) electrode Comby EEG caps, blunt needle, 5ml syringe, and electrolyte gel (Electro-Cap International Inc.). Free, open-source software (Audacity.com) is used to record/playback all auditory rewards during active/sham sessions.
4.	Procedures: Describe each of the procedures, activities, and/or processes used in the intervention, including any enabling or support activities.	Subjects will be asked to arrive with non-braided, clean, dry hair. They will be seated in a comfortable chair with their eyes closed in a quiet, cool (~15°C), dimly lit room. An appropriately sized Comby EEG cap will be affixed to the head and, using a blunt need and syringe, the scalp will be mildly abraded just prior to the application of the electrolyte gel beneath each electrode. EEGs will be recorded with the Ag/AgCl electrodes positioned according to the International 10–20 system (i.e. Fp1, Fp2, F3, F4, C3, C4, P3, P4, O1, O2, F7, F8, T3, T4, T5, T6, Fz, Cz, Pz) using a linked mastoids reference and a ground electrode positioned centrally between, F3, Fp1, Fz and Fpz. Impedances will be kept below 10 kΩ. Immediately prior to each training period, a demonstration of motion/EMG artefact alerts will be provided with instructions to avoid eye/head/face movements to minimize this non-rewarding feedback. Participants will then be instructed to close their eyes, relax, stay awake, and listen to the sound being played. They will be informed that the sound they hear reflects that they are doing well. Continuous, real-time auditory feedback (organ tones) will be used for reinforcement when the subject’s ISFs surpass the threshold(s). The reward threshold will be manually adjusted in real-time to maintain a 60% ± 10% success rate. The yoked-sham sessions will be identical to active sessions, including live EEG recordings and real-time motion/EMG artefact alerts, however the auditory rewards will derive from playbacks of consecutive, pre-recorded sessions of another female with IDs. The trainer will remain present for the duration of all sessions to monitor the EEG.
5.	**Who provided** For each category of intervention provider (e.g. psychologist, nursing assistant), describe their expertise, background and any specific training given.	A non-blinded doctoral student with 2+ years of training and experience in the administration of NFB
6.	**How** Describe the modes of delivery (e.g. face-to-face or by some other mechanism, such as internet or telephone) of the intervention and whether it was provided individually or in a group.	sLORETA ISF-NFB sessions will be performed one-on-one and face-to-face
7.	**Where** Describe the type(s) of location(s) where the intervention occurred, including any necessary infrastructure or relevant features.	sLORETA ISF-NFB sessions will take place in the EEG lab of the Department of Psychological Medicine, University of Otago, Dunedin, New Zealand.
8.	**When and how much** Describe the number of times the intervention was delivered and over what period of time including the number of sessions, their schedule, and their duration, intensity or dose.	Participants will attend three 30-min sessions per week over 4 consecutive weeks (12 sessions in total).
9.	**Tailoring** If the intervention was planned to be personalized, titrated or adapted, then describe what, why, when, and how.	Auditory feedback during active sLORETA ISF-NFB sessions will be based on each person’s real-time EEG-derived cortical ISFs. Thresholds will be manually adjusted, as needed, to maintain the pre-specified feedback success rate (i.e. 60% ± 10%)
10.	**Modifications** If the intervention was modified during the study, describe the changes (what, why, when, and how).	Not applicable. This is a protocol.
11.	**How well** Planned: If intervention adherence or fidelity was assessed, describe how and by whom, and if any strategies were used to maintain or improve fidelity, describe them.	Protocol adherence will be monitored by the trainer. Attempts will be made to mitigate adherence issues via automated email and text message reminders sent on the day of each training session.
12.	Actual: If intervention adherence or fidelity was assessed, describe the extent to which the intervention was delivered as planned.	Not applicable. This is a protocol.

### Participant timeline

The trial period for each participant will be approximately 10 weeks and consist of one 30-min screening interview, two 60-min baseline assessments approximately 1 week apart, six 30-min genuine or sham ISF-NFB sessions (3× per week over 2 consecutive weeks) starting within 1 week after baseline #2, a 60-min post 6 sessions assessment, six 30-min genuine ISF-NFB sessions (3× per week over 2 consecutive weeks), a 60-min post 12 sessions assessment, and a 60 min 1-month follow-up assessment (Table 2 and Fig. 2). All post-treatment assessments and procedures will be identical to those performed at baseline.

**Table 2 Tab2:** Schedule of enrollment, interventions, and assessments

	T0	T1	T2	Allocation	T3-8	T9	T10-15	T16	T17
Enrollment									
Eligibility screen (MINI)	✓								
Informed consent	✓								
Anthropometric measures	✓								
Assessments									
PROs		✓	✓			✓		✓	✓
EEG		✓	✓			✓		✓	✓
ECG		✓	✓			✓		✓	✓
DESS					✓		✓	✓	✓
Blinding integrity						✓			
Groups									
Active	✓	✓	✓	✓	✓	✓	✓	✓	✓
Sham	✓	✓	✓	✓	✓	✓			

*Abbreviations*: *MINI* Miniature International Neuropsychiatric Interview, *PROs* patient-reported outcomes, *EEG* electroencephalography, *ECG* electrocardiography, *T0* interview, *T1* baseline #1, *T2* baseline #2, *T3–8* neurofeedback sessions 1 through 6, *T9* post 6^th^ session assessments, *T10–15* neurofeedback sessions 7 through 12, *T16* post 12^th^ session assessments, *T17* 1-month follow-up assessments

**Fig. 2 Fig2:**
[figure not shown]
Flow chart of enrollment, assessments, and interventions. Abbreviations: MINI, Mini International Neuropsychiatric Interview; ISF1, 1-region Infraslow Neurofeedback; ISF2, 2-region Infraslow Neurofeedback

### Criteria for discontinuing or modifying allocated interventions

Participants will be advised that they were able to withdraw at any time without giving a reason or may be withdrawn by the lead investigator if they (1) experience significant adverse effects that were deemed detrimental to their well-being or (2) are unable to adhere to protocol (e.g. missed >1 training session in either 6 session block, started or modified first-line therapies).

### Strategies to improve adherence to interventions

We will attempt to mitigate adherence issues via automated email and text message reminders sent on the day of each training session.

### Plans to promote participant retention and complete follow-up

Once enrolled, every reasonable effort will be made to follow participants throughout the entirety of the study period via ongoing email and text messaging correspondence. In the event of premature discontinuation of the study for any reason, participants will be made aware that all data collected up to the point of withdrawal may be used for analyses.

### Relevant concomitant care permitted or prohibited during the trial

Participants were asked to maintain any current first-line mental health therapies (e.g. pharmacotherapy) for the entire length of the trial period (i.e. baseline through follow-up). Any changes or introductions of first-line therapies (e.g. altered pharmacotherapy dosages, introduction of intensive psychotherapy) will render participants ineligible.

### Provisions for post-trial care

In the unlikely event of injury, participants will be eligible to apply for compensation from the Accident Compensation Corporation (ACC) of New Zealand just as they would be if they were injured in an accident at work or at home. Although there are private providers abroad (e.g. Asia, North America, and Europe), should this trial provide evidence of efficacy, there is currently no access to this therapy within New Zealand.

### Measurements

#### Primary outcomes: HADS, fb-EEG

The central importance of PROs in clinical trials has been emphasized by both international health regulatory agencies and patients [216, 217], therefore, the *primary* outcome of interest will be the HADS [218, 219]. Additionally, the importance targeted EEG-learning assessments in NFB trials has been emphasized by researchers [120–126], therefore activity (i.e. amplitude of the oscillations) and connectivity (i.e. coordinated amplitude and/or phase of the oscillations) changes within and between the targeted ROIs will also be of primary interest. Primary outcome measures will be collected at baseline, post 6 sessions, post 12 sessions, and 1-month follow-up.

##### Hospital anxiety depressions scale (HADS)

The HADS is a valid and reliable 14-item, trans-diagnostic PRO measure used to assess anxiety and depression severities [218]. Response options are on a 4-point scale (0–3) based on participants experiences over the past week with anxiety and depression subscale scores graded as follows: 0–7 = ‘normal’, 8–10 = ‘mild’, 11–14 = ‘moderate’, and 15–21 = ‘severe’ [220]. The HADS has been repeatedly shown to be a reliable and valid tool across a variety of settings [219, 221, 222]. There is some debate with respect to whether the HADS is best assessed via the total 14-item score [223–225] or two 7-item subscale (anxiety and depression) scores [219, 222, 225, 226]. For our trial, we are considering the anxiety (HADS-A) and depression (HADS-D) subscale scores separately. Importantly, the minimum clinically important difference (MCID) for the HADS subscales is estimated to be a reduction of 1.5 to 2 points [227–229].

##### Full-band EEG (fb-EEG)

The use of full-band EEGs permits the non-invasive examination of the entire spectrum of brain frequencies from infraslow (<0.1 Hz) to gamma (>30 Hz) using scalp-recorded electrical signals acquired from direct current (DC) coupled amplifiers. Further, source-localization software can locate the probable generators (i.e. brain sources) responsible for the acquired electrical signals, thereby permitting us to assess activity (i.e. log-transformed current source density; log-CSD) and connectivity (i.e. lagged linear connectivity; lag-CON). EEG pre-processing will be performed offline using EEGLAB version 14.1.1 [230] and ERPLAB version 6.1.4 [231] running on MATLAB 2021a (The MathWorks, Inc., Natick, MA, USA.). Custom scripts developed in MATLAB utilizing EEGLAB, ERPLAB, and MATLAB functions will be used. The raw EEG will be imported into MATLAB using EEGLAB. Channel locations/coordinates will be determined via EEGLAB’s *Montreal Neurological Institute (MNI) coordinate file for BEM dipfit model* with the head centre optimized. Non-EEG (i.e. VEOG, HEOG, EKG, EMG, GSR) and four EEG (i.e. F11, FT11, F12, and FT12) channels will then be removed prior to manual co-registration used to match the coordinates of the 60 remaining channels to the realistic *Boundary Element Model (MNI)* head model*.* Of note, the four EEG channels selected for removal lack locations in the MNI coordinate file, thereby precluding subsequent pre-processing. The data will then be truncated to retain only the middle 600-s of the time-series, and the PREP pipeline version 0.55.1 [232] will be run to identify and interpolate bad channels, remove line noise, and robust average reference the data. This pipeline has been used previously for evoked potentials and resting-state EEG data [233, 234]. PREPed EEGs with >25% (i.e. >15) bad channels identified will not be considered for further analyses. For identification and marking of artefact-contaminated epochs, continuous PREPed EEGs will be 1 Hz high-pass filtered using a finite impulse response (FIR) filter implemented using EEGLAB’s pop_firwsord function (window = Kaiser 5.653, transition bandwidth = 1.5 Hz, max ripple = 0.001, order = 2416) and segmented into 1-s epochs. Epochs will automatically be marked as artefacts if containing one or more of the following characteristics: (i) absolute voltage exceeds 100 μV, (ii) peak-to-peak voltage exceeds 150 μV in any sliding window of 200 ms width with a step size of 100 ms, (iii) voltage greater than 100 μV resulting from a step-function with a sliding window 200 ms wide with a step size of 50 ms, (iv) sample-to-sample difference exceeding 50 μV, or (v) absolute voltage less than 1 μV for 150 ms (i.e. flat-lined data). Following this, manual verification/correction of epoch classifications (i.e. artefact and non-artefact) will be performed. Manually verified time-series with >50% (i.e. >5 min) artefact-contaminated epochs will be excluded from further analyses. For independent component analysis (ICA), the data will again be 1 Hz high-pass FIR filtered (window = Kaiser 5.653, transition bandwidth = 1.5 Hz, max ripple = 0.001, order = 2416), down-sampled to 500 Hz to reduce computation time, have noisy channels and artefact-contaminated epochs removed, and decomposed into maximally independent components (ICs) which are spatially fixed and temporally discrete [235] using adaptive mixture ICA (AMICA) [236]. AMICA was selected based on its superior performance when compared with other ICA algorithms [237]. The resulting ICA weights will be applied to 1–100 Hz band-pass FIR filtered (window = Kaiser 5.653, transition bandwidth = 1 Hz, max ripple = 0.001, order = 3624) data. We will use ICLabel [238] with manual verification to categorize the ICs as brain or other (i.e. muscle, eye, channel noise, line noise, or other) based on their spatial distribution (scalp topography), time course, spectrograms, event-related potential (ERP) images, and current dipole models using recommendations from Jung et al. [239], Chaumon et al. [240], and the website https://labeling.ucsd.edu/. Finally, bad ICs will be removed, noisy channels interpolated, and the data 0.01–100 Hz bandpass infinite impulse response (IIR) filtered (1^st^ order Butterworth) to give cleaned datasets. This IIR filter has been utilized in previous studies of eISFs [80, 241]. Finally, cleaned datasets with ICA will be downsampled to 128 Hz to reduce computation time and exported to ASCII text files for subsequent analyses. Figure 3 shows an overview of the EEG pre-processing pipeline.

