Following completion of their PROs, neurophysiological data will be collected from each participant using Compumedics Neuroscan SynAmps RT 64-channel amplifier (DC mode, input impedance >10 GΩ, 24-bit analogue-to-digital resolution, common mode rejection >110 dB) using a continuous sampling rate of 1000 Hz. Recordings will take place in a quiet, cool (~15°C), dimly lit room as participants are seated upright in a comfortable chair with their eyes closed. We chose the eyes-closed condition because it has been reported to improve EEG reliability [200, 201]. The 10.5 min resting-state full-band EEGs (fb-EEGs) will use high-density (64-channel) silicone Quik-Cap Hydro Net caps with Ag/AgCl electrode placements corresponding to the international extended 10/20 system. The ground electrode is positioned at AFz with the reference electrode midway between Cz and CPz. Electrooculography (EOG) will track vertical and horizontal eye movements. The cap is soaked in a saline solution at least 30 min prior to application and all electrode impedances will be kept below 10 kΩ. To help reduce impedances, subjects will be asked to arrive with non-braided, dry, clean (i.e. no conditioner, gels, pastes, or sprays) hair. Concurrent with the resting-state EEG, a spontaneous breathing standard limb lead (lead-II) electrocardiogram (ECG) using Ag/AgCl electrodes will be performed. Following, a 10 min metronome paced breathing (12 breaths per minute) ECG with a 1:1 inspiratory/expiratory (I/E) ratio (i.e. 2.5-s inhalation/2.5-s exhalation) was collected. During pacing, participants will be instructed to breathe through their nose at normal depth (i.e. no deep breathing).

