
**Fig. 3 Fig3:**
[figure not shown]
Overview of EEG pre-processing pipeline. FIR, finite impulse response; IIR, infinite impulse response; ICA, independent component analysis; AMICA, adaptive mixture ICA; ICs, independent components; Hz, Hertz

Via LORETA-KEY software (v20210701, freely available at http://www.uzh.ch/keyinst/loreta.htm), ASCII text files will be used as input to compute cross-spectral matrices for each participant for seven frequency bands (infraslow 0.01–0.1 Hz; slow 0.2–1.5 Hz; delta 2–3.5 Hz; theta 4–7.5 Hz; alpha 8–12 Hz; beta 12.5–30 Hz; gamma 30.5–44 Hz) utilizing fast Fourier transform (FFT). To allow for 2 complete cycles of the lowest frequency of interest (i.e. 0.01 Hz) and to obtain smooth power spectral density, EEGs will be segmented into 200-s epochs with Hanning (Hann) tapered windows applied. The cross-spectral matrices will then be averaged for each subject and used as input to exact LORETA (eLORETA) to compute whole-brain current source density (CSD; A/m^2^) without assuming a pre-defined number of active sources [242, 243]. Using the MNI-152 (Montreal Neurological Institute, Canada) template, eLORETA produces an inverse solution space consisting of 6239 cortical grey matter voxels at 5 mm resolution and has been shown to produce exact, zero-error localizations even in the presence of measurement and structured biological noise. eLORETA performs voxel-by-voxel between-condition comparisons of the CSD distribution. Statistical non-parametric mapping (SnPM) will be performed for each contrast using built-in voxel-wise randomization test (5000 permutations) to calculate the empirical probability distribution for the max-statistic (e.g. the maximum of a *t* or an *F* statistic) under the null hypothesis while correcting for multiple testing (i.e. for the collection of tests performed for all electrodes and/or voxels, and for all time samples and/or discrete frequencies). For each contrast, the voxel-level, two-tailed max-statistic was used as input to LORETA-KEY software to identify and visualize differences/changes in log-CSD for each of the seven frequency bands. Furthermore, for each condition, log-CSDs were averaged across all voxels within a 10-mm radius of the centre of mass MNI coordinates derived from previous literature [244] of the targeted ROIs (Fig. 4). This output was exported to Excel (version 2112) and analysed in R (version 4.0.5 [245];) to identify differences/changes in log-CSD between contrasts for each ROI in each frequency band. Next, functional connectivity (FC; i.e. lag-CON [242]) between the targeted ROIs was calculated for each group at each time point in LORETA-Key. Output was then exported to Excel and analysed in R to identify differences/changes between contrasts in each frequency band. Finally, as effective connectivity (EC) reflects directed functional connectivity, significant ROI pairs identified from FC analyses were selected for EC (i.e. Granger causality [246]) analyses. As with FC, EC was calculated in LORETA-Key, exported to Excel, and analysed in R.

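### The 50% artefact rule, set on 1-s epochs of 1 Hz high-passed data, does not test data quality in the trained 0.01–0.1 Hz band, whose spectra use 200-s epochs

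*Protocol article*

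**What the plan says.** All of this is in the protocol article. Under Baseline assessments, the resting recording lasts 10.5 min. Under Full-band EEG (fb-EEG), "The data will then be truncated to retain only the middle 600-s of the time-series". These data are high-pass filtered at 1 Hz ("max ripple = 0.001, order = 2416) and segmented into 1-s epochs"), and five voltage criteria mark artefact epochs, followed by manual checking. The acceptance rule is: "Manually verified time-series with >50% (i.e. >5 min) artefact-contaminated epochs will be excluded from further analyses".

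Marked epochs are said to be removed at one step only, in the copy prepared for the ICA decomposition: "have noisy channels and artefact-contaminated epochs removed, and decomposed into maximally independent components (ICs". The dataset that goes forward is described separately: "Finally, bad ICs will be removed, noisy channels interpolated, and the data 0.01–100 Hz bandpass infinite impulse response (IIR) filtered". No epoch rejection is stated there.

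The same section then sets the spectral window: "To allow for 2 complete cycles of the lowest frequency of interest (i.e. 0.01 Hz"), "EEGs will be segmented into 200-s epochs with Hanning (Hann) tapered windows applied". Cross-spectra are averaged per subject over whatever epochs exist. Infraslow is one of seven bands. Under Primary outcomes, activity and connectivity in the targeted regions are of primary interest alongside the HADS. Under Intervention descriptions, the trained signal is the infraslow one.

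**The concern.** The acceptance rule and the spectral estimate work on different time scales and in different frequency ranges. A count of bad seconds above 1 Hz says little about whether a 200-s stretch is sound at 0.01–0.1 Hz. Slow drift below 0.1 Hz is not screened by the five automatic criteria, because the 1 Hz filter has already removed it. Conversely, a recording can pass with half its seconds marked.

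This matters most in the band that the intervention trains, with about 15 participants per active arm. The exposed analyses are those that compare visits within the active groups (Objectives 3 and 4) and the regression of HADS change on change in regional activity and connectivity (Objective 2). Someone who becomes calmer and stiller may have fewer marked seconds and better symptom scores together. An infraslow measure that responds to contamination would then show an association without any change in the brain.

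**Working it through.** **Inputs from the document.** Recording 10.5 × 60 = 630 s; analysed length 600 s; marking epoch 1 s; acceptance limit 50%; spectral epoch 200 s; infraslow band 0.01–0.1 Hz. No overlap between windows and no minimum number of 200-s epochs is stated.

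**The plan's own figures reproduce.** 0.50 × 600 s = 300 s = 5 min. Two cycles at 0.01 Hz: 2 / 0.01 = 200 s.

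**Literal reading: nothing is cut from the cleaned data.** Epochs = 600 / 200 = 3 for every accepted recording. Up to 300 s may be marked. One 200-s epoch could be wholly marked (200 s) and another half marked (100 s), and the recording would still pass. The ICA that cleans those seconds was fitted to 1 Hz high-passed data from which they had been removed.

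**Alternative reading: marked seconds are cut and the rest joined.** Epochs = floor(clean seconds / 200).

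| Marked | Clean | 200-s epochs |
|---|---|---|
| 0 s | 600 s | 3 |
| 1 to 200 s | 599 to 400 s | 2 |
| 201 to 300 s | 399 to 300 s | 1 |

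A single marked second takes the count from three to two. Joining also compresses time: removing a fraction p in scattered seconds multiplies apparent frequency by about 1/(1 − p), so at p = 0.5 a 0.06 Hz rhythm would appear near 0.12 Hz, outside the band.

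**Effect of epoch count.** The document gives no spectra, so these are assumptions: two unrelated signals with spectra 1/f^0, 1/f^1 and 1/f^2, Hann windows of 200 s, and bins 0.005 Hz apart, which gives (0.1 − 0.01)/0.005 + 1 = 19 bins. Cross-spectra are pooled over the band; 3,000 draws per case.

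| Spectrum | SD of log power, 1 / 2 / 3 epochs | Variance ratio, 1 vs 3 | Null lagged connectivity, 1 / 2 / 3 epochs |
|---|---|---|---|
| 1/f^0 | 0.322 / 0.223 / 0.181 | 3.2 | 0.049 / 0.025 / 0.017 |
| 1/f^1 | 0.388 / 0.268 / 0.223 | 3.0 | 0.074 / 0.038 / 0.025 |
| 1/f^2 | 0.564 / 0.415 / 0.339 | 2.8 | 0.159 / 0.084 / 0.057 |

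Null connectivity at one epoch against three is 0.049/0.017 = 2.9, 0.074/0.025 = 3.0 and 0.159/0.057 = 2.8 times higher.

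**Effect of overlap.** With 50% overlap, the same 600 s gives (600 − 200)/100 + 1 = 5 windows. In the 1/f case with a first-order 0.01 Hz high-pass, the SD of log power falls from about 0.20 to 0.16, so the variance falls by 1 − (0.16/0.20)² = 36%. Null lagged connectivity falls from about 0.021 to 0.013–0.014. A rerun across all three spectra, with and without that filter, gave variance reductions of 34% to 37%. The gain arises because the Hann taper almost discards data near the window edges, and overlapping windows recover them.

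**The case against.** The strongest reply is that cutting and joining is not in the text. Contaminated epochs leave only the copy used to fit the ICA; the cleaned dataset comes from component removal, channel interpolation and filtering. On that reading every accepted recording has three epochs, counts are equal across visits and arms, and both the epoch-count figures and the frequency compression drop out. This stands, and it is why the retained marked seconds come first here and the cutting reading second.

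Second, a second marked above 1 Hz is not shown to be artefact at 0.01–0.1 Hz, and components judged bad have been removed. That is fair: these are marked seconds, not known infraslow artefact. But the same fact means that the rule does not test the trained band in either direction.

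Third, a reader might infer bias between arms because trainees practise staying still. The document does not support this. Under Who will be blinded? and Intervention descriptions, sham participants have live EEG and the same real-time artefact alerts. A shift common to all arms would not bias the between-group contrast of Objective 1.

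Fourth, the article is condensed, its pipeline figure is not shown, and custom scripts may settle the point. However, the section gives this pipeline down to filter order, and the two rules it does state do not fit each other for the infraslow band.

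**Conclusion.** The concern holds in limited form. The one acceptance rule for time segments is not a quality check for the infraslow band. On the literal text, up to half of an accepted recording's infraslow data may be marked seconds. How much that moves the estimates cannot be computed, because no contamination rate is given and 50% is the worst accepted case. If marked seconds were cut, the cost at one epoch against three is about threefold in log-power sampling variance and in null lagged connectivity. Those figures rest on assumed spectra, though the ratios were similar for all three.

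The result is extra noise, plus bias where contamination changes between visits or moves with symptoms (Objectives 2 to 4). A reader might conclude that accepted recordings cannot be compared across visits or arms. That does not follow: counts are equal on the literal reading, and on the other reading comparison is weakened but not ruled out. Nor does the 50% rule create the ceiling of three epochs, which comes from 600 s and 200-s windows without overlap. The faster bands have many cycles per window and are little affected.

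**What to change.** For the infraslow band only:

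1. State that the 600 s stay continuous, with no cutting and joining.
2. Use 200-s Hann windows with 50% overlap, five per recording.
3. Set a limit on marked seconds per 200-s window, fixed before group comparisons are made.
4. Base power and lagged connectivity on the same number of windows for every participant and visit. Where that number is not reached, set the infraslow value to missing.
5. Report marked seconds by visit and arm.

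Keep the 50% rule for the faster bands. Interpolating marked seconds is best kept as an optional sensitivity analysis, because it can distort heavily marked records.

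The cost is a script change on stored recordings and a few sentences in the protocol; no new recordings are needed. The downside is that heavily contaminated recordings lose their infraslow value. These should be few, but the number cannot be stated in advance without a contamination rate.
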